## Abstract

**Background::**

People with atypical parkinsonism, such as multiple system atrophy and progressive supranuclear palsy, experience a wide range of motor and non-motor symptoms associated with the increasing complexity of care delivery and the increased risk of complications and hospital admissions.

**Objectives::**

To investigate the efficacy and cost-effectiveness of a 12-month remote home-based integrated program aiming to improve healthcare delivery coordinated by a nurse specialized in the management of individuals with atypical parkinsonism (parkinsonism nurse specialist, PKNS) compared to the standard-of-care model.

**Design::**

Multicenter, randomized, single-blind, controlled clinical trial involving 164 individuals with atypical parkinsonism.

**Methods and analysis::**

Participants will be randomized 1:1 in intervention (PKNS) and control (standard-of-care) arms. Assessments will be undertaken at baseline and after 6 and 12 months. Primary outcome measure is the Parkinson’s Disease Questionnaire 39-items scale total score. Secondary measures include the clinical scales testing motor and non-motor symptoms, caregiver burden, adherence to therapy, cumulative disease burden and the number of unplanned hospital visits/admissions during the study period. The cost-effectiveness of this method will be evaluated by using the EuroQoL-5, which estimates the incremental cost per quality-adjusted life-years gain. Real-life motor autonomy will be objectively measured by collecting waist-worn wearable data on gait parameters (automatically detecting motor patterns indicative of freezing of gait and falls) in all subjects for five consecutive days each month during the 12-month duration of the study.

**Ethic::**

Study protocol has been approved by the ethics committee of all participating centers. The study is conducted according to good clinical practice and the Declaration of Helsinki.

**Discussion::**

An integrated remote care model at home coordinated by a specialized nurse in the management of parkinsonism (Telenursing) could offer significant benefits to patients and healthcare professionals through better health education, continuity of care, and careful monitoring of complications.

**Trial registration::**

ClinicalTrials.gov identifier NCT05792332.

## Background

Parkinsonism (PKS) refers to a clinical syndrome characterized by bradykinesia, rigidity, gait, and postural disturbances. People living with parkinsonism (PwP) experience a wide range of motor and non-motor symptoms and high complexity in care management, inevitably leading to significantly higher disability and burden on healthcare resources. Therapeutic intervention in PwP goes beyond pharmacological therapy by integrating a wide variety of interventions typical of nursing management, and it aims at ensuring greater control of motor symptoms (e.g., prevention of falls and bone fractures) and non-motor symptoms (e.g., dysphagia, orthostatic hypotension, constipation, micturition disorders, sleep disorders, etc.) and the maintenance of functional autonomy. These are two fundamental prerequisites to achieve the goal of adequate management of chronic neurodegenerative diseases.

An integrated approach, involving a nurse specialized in parkinsonism (parkinsonism nurse specialist, PKNS) alongside a neurologist could offer significant benefits to patients and care providers through improved health education, continuity of care, and prevention and close monitoring of incident complications.^1,2^ Several studies highlight how a multidisciplinary approach including a PKNS can offer significant benefits to patients and care providers in the management of disability caused by motor and non-motor symptoms and in monitoring side effects and adherence to therapy.^3,4^ A PKNS may be the most suitable candidate to the “first point of access” for queries raised by patients and/or care partners and create a filter for the different assistance requests through a triage and dedicated referral.^
2
^ In a hub-and-spoke model, the PKNS may be the joining link between a tertiary referral center (“hub”) and nearby community hospitals (“spoke”). PKNS can play a fundamental role in shifting and sharing tasks in the management of people with PKS, significantly contributing to alleviating the care burden on neurologists. In this scenario, the PKNS may be defined as “case manager” who can filter assistance requests and independently manage many motor and non-motor problems to involve the neurologist only if necessary. In several regions such as the UK,^5,6^ nurses are granted the authority to prescribe medicines and play a vital role in maintaining continuity of care for chronic diseases by coordinating care between patients and primary and secondary care providers.^
7
^ Guidelines for PD nurse specialists have been developed in UK, the Netherlands, and Germany,^1,3,8^ whereas is Italy the value and the authority of the PD nurse specialist is still under-recognized and we feel that a cultural evolution is urgently needed.

In the absence of specialized support, patients and/or care partners may either underestimate symptoms that require immediate therapeutic intervention or overestimate them and increase utilization of healthcare resources by unnecessary emergency room visits and consultations and greater number of hospitalizations. Falls, urinary infections, and dementia account for 24%, 16%, and 13% of emergency room access costs, respectively.^
9
^ Disease progression leads to increased risks of morbidity and subsequent mortality from complications due to motor disability (e.g., falls, fractures, dysphagia, infections) and non-motor disability (e.g., dementia, psychosis, dysautonomia). When patients with parkinsonism are hospitalized, the length of stay increases,^
10
^ the risk of infections, prescribing errors, increased postoperative mortality^11,12^ with increased risk of re-hospitalization.^
13
^ A study in the United States reported a significant economic burden due to hospitalization of patients with parkinsonism: about 20% of the estimated annual cost per patient ($4.6 billion US) was due to hospital costs.^
10
^ Several retrospective studies have shown that frequent neurological consultations and adherence to the drug therapy schedule can reduce hospitalization by up to 50%.^
12
^ Falls, fractures, infections, and cognitive and motor decline have been identified as risk factors for unplanned hospitalizations in patients with parkinsonism.^12,13^ These complications are more frequent in primary atypical parkinsonism such as multiple system atrophy (MSA) and progressive supranuclear palsy (PSP) than in PD, because of the greater extent and rapidity of the neurodegenerative process, the reduced efficacy of drug therapy or more common drug-related side effects. Given the magnitude of hospitalizations in PwP, associated morbidity, mortality, and healthcare-related costs, there is a need for cost-effective interventions to reduce unplanned hospitalization by acting on preventable risk factors.^
14
^ Optimizing clinical management of motor and non-motor symptoms and pharmacological side effects, through a telenursing service may prevent falls and hospital admissions, with an increased quality of life and a reduction of comorbidity and risk of caregiver’s burnout.

## Rationale

The aim of the IMPACT project is to measure the effectiveness of a specialized healthcare model governed by a case manager via telemedicine dedicated to coordinating the care activity offered to patients with atypical parkinsonism in comparison with the standard-of-care model in terms of improving the quality of life. To date, no study has ever reported the effectiveness of a telemedicine service managed by a PKNS who take care of the patient by telephone and follow an Integrated Care Plan (herewith defined as “Telenursing”).

The IMPACT project is designed to investigate the benefits and cost-effectiveness of an integrated patient-centered care to propose this model to stakeholders as a new pragmatic organizational model to foster continuity of care by exploiting the potential of existing care resources. This model implements a personalized telenursing-based approach with the patient at home, including through a passive telemonitoring system of the patient’s mobility and risk of falls. As an alternative to the usual clinical model of care, in this model people with parkinsonism are proactively followed remotely by a PKNS, who can prevent and minimize complications caused by the disease and/or medication side effects (e.g., falls and fractures caused by instability or orthostatic hypotension) by promoting flexible, personalized, and comprehensive care. It is expected that this telenursing-based model will simplify care delivery by reducing the incidence of complications and unplanned hospital admissions.

Many elements of the IMPACT innovative and timely design can be widely implemented in different healthcare settings and become part of our new way of managing patients with chronic neurological diseases, including but not limited to patients with rare, atypical parkinsonism. We will use a semi-structured flowchart that the case manager follows (1) to create a “tailor-made” file of the patient on entry to the practice, (2) proactively follow up on the most relevant motor and non-motor problems to prevent complications, and (3) to use a flowchart predefined by nurses to organize incoming calls (reactive action) and define the triage code to alert the neurologist and general practitioner for activation of the multidisciplinary team. The application of new wearable sensors and advanced machine learning algorithms will objectively monitor the real-life autonomy motor in a home environment and further indicate the innovative aspect of our research project.^
15
^ Efficacy will be assessed both by estimating the improvement in quality of life and coping mechanisms related to motor and non-motor disorders and by weighing the reduction in any unplanned hospital admissions (e.g., requests for unplanned “extra” neurological visits, any hospital or emergency room admission).

## Methods and analysis

### Study design

Multicenter case-control, nonprofit, randomized 1:1, single-blind, parallel-group clinical trial to recruit 164 patients (*n* = 82 per arm) with atypical parkinsonism (MSA or PSP) from the four operating units involved. The study duration per single patient will be 12 months. The study sites include Fondazione IRCCS Istituto Neurologico Carlo Besta (Milan), IRCCS Mondino Foundation (Pavia), IRCCS Istituto Neurologico Mediterraneo Neuromed (Pozzilli), and Gaetano Martino University Hospital (Messina).

The study has been approved by each centers Ethics Board (Protocol ID: IMPACT). The trial has been registered on ClinicalTrials.gov (ID: NCT05792332).

### Recruitment and participants

Participants must fulfill the following inclusion criteria: (1) age 40–85 years and (2) clinical diagnosis of MSA^
16
^ or PSP^
17
^ in all their possible variants (MSA of parkinsonian vs cerebellar type;^
16
^ PSP Richardson Syndrome, PSP-Parkinsonism, PSP-Corticobasal Syndrome, etc.^
17
^) according to internationally validated criteria. Exclusion criteria include: (1) Hoehn and Yahr stage 5 in ON phase (bedridden patients); (2) Clinical Frailty Scale (CFS) ⩾ 8^
18
^; (3) dementia according to Diagnostic and Statistical Manual of Mental Disorders 5th edition (DSM-V) criteria; and (4) serious medical disorders that, in the opinion of the recruiting neurologist, may impair participation in the study.

Potential participants will be recruited at each center. Individuals referred to the study will be pre-screened via chart inspection and offered a screening visit if they meet inclusion criteria. At the screening visit, the inclusion and exclusion criteria will be reviewed. Participants are consecutively enrolled by the investigating neurologist of the participating centers after obtaining and signing an informed consent form. Forms for registering patients evaluated for possible study participation and those enrolled must be completed and kept by each experimental center (with a copy to the sponsor). A form for identification of all patients (with study code and patient identification data) who were screened for the study should be completed and filed at the center (Subject Identification Code List).

Then, participants’ demographic information, medical history, and concomitant medication list will be recorded. Contacts and minimum clinical data useful for stratification (see below) will be addressed to the Clinical Research Coordinator (CRC) of the coordinating center.

### Randomization and blinding

Eligible patients will be randomized with 1:1 allocation into the two treatment arms with a centralized web-based randomization system. The randomization list will be generated by computer. Randomization is stratified by (1) sex, (2) diagnosis (MSA vs PSP), and (3) disability (CFS ⩽ 4 vs. > 4). For blinding purposes, the CRC schedules evaluation by a blind neurologist (“blind rater”) of all enrolled patients, blind to randomization. The blind rater will perform the scales and questionnaires prescribed in the protocol. The patient knows if he/she will follow the “case-manager” procedure or if he/she will be approached with the standard-of-care model.

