### Intervention and monitoring

#### Intervention arm

Patients in the intervention arm will receive care from a PKNS for any medical (non-administrative) needs tailored to their necessities and standard medical treatment. A PKNS from each site will follow the patients enrolled.

- *PROACTIVE monitoring*: At baseline (V1), the PKNS contacts the patient to create a personal record using a semi-structured interview, including all symptoms of motor and non-motor characteristics and the type of risks that may occur. The PKNS instructs on risk prevention strategies related to the most relevant issues reported. After the initial proactive call to V1, PKNS will provide intermediate contacts every 3 months. At intermediate calls (V2, V3, V4), the PKNS focuses the interview on the problems/risks detected at baseline and provides tailored counseling and education. At the final visit (V5), the investigator will complete the follow-up of all the incident events and medical issues occurred during the study.- *REACTIVE monitoring*: During the study period, the patient and care provider may contact the PKNS at any time prior to the previously scheduled in-person visit for urgent needs by telephone (3h/day, 5 days/week, Mon-Fri) or by e-mail (within 48 h).

The PKNS can (1) also address the specific problem by interacting with the participant’s primary care physician and other healthcare providers or (2) refer to the treating neurologist (who is not the blind rater) for teleconsultation or in-person visit, according to a semi-structured algorithm that assigns four levels of priority similar to emergency room “triage”.^
19
^ Briefly, whenever a referral to a neurologist is needed, PKNS assigns a 4-level code triage, where increased urgency would lead to reduced assessment time and the opportunity for a teleconsultation with an experienced neurologist. We proposed this approach to triage patients query during COVID-19 pandemic, including a detailed flowchart.^
19

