#### Control arm

Patients in the control arm will undergo a 30-min in-person visit with the neurologist at baseline (V1), 6 months (V3), and 12 months (V5) after randomization.

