### Analysis plan

#### Simple size

This is the first study to investigate the efficacy of an integrated program in patients with rare forms of parkinsonism such as MSA and PSP, whereas this has been previously studied only in PD.^
4
^ Considering that there is no validated questionnaire measuring quality of life in MSA and/or PSP, we relied on data from a previous randomized trial on the effectiveness in terms of health-related quality of life of an integrated program coordinated by a case manager versus the standard of care in PD.^
4
^ We hypothesized a difference of at least 3, 9 in change at 12 months in the PDQ-39 between the proposed integrated care model and the standard of care, with expected standard deviations of 8.6 in the control group and 5.8 in the treated group. Considering a type I error of the two-tailed *t*-test of 5%, a power of 90% and a loss to follow-up of no more than 10%, a sample size of 164 patients (82 per arm) is needed. Although patients with MSA and PSP are expected to show a more aggressive disease course than PD with a more rapidly worsening course of disability and quality of life than idiopathic PD, we decided to maintain a similar effect size to compensate for the potential lower specificity of the primary outcome measure (e.g., PDQ-39).

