#### Statistical analysis

No intermediate analysis is planned. The primary analysis will be by intention to treat principle as far as is practically possible. Analysis by protocol (PP) will be done after excluding patients with major deviations from the protocol. Descriptive statistics by treatment arm will be provided for all variables assessed in the study protocol with mean and standard deviation and median with range for continuous variables and absolute numbers and percentages for categorical variables.

The primary analysis will be based on the two-tailed *t*-test. Changes from baseline in the primary and secondary continuous variables (including longitudinal data obtained from the wearable device) will be analyzed by analysis of variance for repeated measures adjusted for baseline, or a corresponding nonparametric analysis as appropriate. Safety analysis will be performed by calculating the proportion of patients with AEs. The *p* values < 0.05 will be considered statistically significant, and all tests will be two-sided. The STATA Statistical Software, Release 16 (StataCorp. 2019. Stata Statistical Software: Release 16. College Station, TX: StataCorp LLC) will be used for statistical analysis.

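### Centre is absent from both the strata and the primary t-test although each of four sites uses its own nurse; adding centre to the model cheaply protects precision, with no bias to correct.

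*Protocol article*

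**What the plan says.** All places are in the protocol article.

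- **Study design:** 164 patients, 82 per arm, are recruited "from the four operating units involved".
- **Randomization and blinding:** allocation is 1:1, "with a centralized web-based randomization system". The strata form a closed, numbered list: "Randomization is stratified by (1) sex, (2) diagnosis (MSA vs PSP), and (3) disability (CFS ⩽ 4 vs. > 4"). Centre is not among them.
- **Intervention arm:** "A PKNS from each site will follow the patients enrolled". The person delivering the intervention therefore changes with the site.
- **Control arm:** the article sets half-hour neurologist appointments, face to face, at entry, month 6 and month 12. Nothing else about standard care is fixed.
- **Statistical analysis:** "The primary analysis will be based on the two-tailed *t*-test". Changes in the primary and secondary continuous variables also "will be analyzed by analysis of variance for repeated measures adjusted for baseline". The baseline value is the only adjustment named.
- **Simple size:** the calculation uses a difference and two SDs, with no allowance for centre.

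**The concern.** The treatment is a way of organising care, delivered by local staff on top of local services. Who the nurse is, how easily a neurologist can be reached and what the nearby hospital offers could all affect quality of life over a year. Centre is thus a plausible predictor of the primary outcome. It is equally plausible for unplanned visits and admissions.

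Nothing keeps the arms balanced within a site, and a two-sample t-test has no place for a centre term. Any between-site variation stays in the error, and in the single trial actually run one arm may hold more patients from a site that does better or worse. At stake is some precision, plus the credibility of a table showing uneven arms within a site. The article also puts the model forward for wider use, so readers will want to see whether one site's nurse carries the result.

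**Working it through.** **1. The plan's own figure.** Inputs from the sample-size section: difference 3.9 ("We hypothesized a difference of at least 3, 9 in change at 12 months in the PDQ-39"), SDs 8.6 and 5.8, two-sided 5%, power 90%, loss 10%.

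- Mean variance = (8.6² + 5.8²)/2 = (73.96 + 33.64)/2 = 53.8, so SD = 7.33.
- n per arm = 2 × (1.960 + 1.282)² × 53.8 / 3.9² = 74.3.
- Allowing for loss: 74.3/0.9 = 82.6, or 74 × 1.1 = 81.4, which rounds up to 82. The stated 82 per arm reproduces, with no centre term.

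**2. Size of the chance imbalance.** With 148 evaluable patients (164 × 0.9 ≈ 148) and no centre stratum, simulation gives the departure from 50% of one arm's share at the worst-balanced site. Site sizes are assumed, because the article gives none.

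| Site sizes | Median | 95th percentile |
|---|---|---|
| 37/37/37/37 | 9.5 points | 17.6 points |
| 74/34/24/16 | 12.5 points | 25 points |

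**3. Effect on the planned t-test, by hand.** Let s be the between-site SD of PDQ-39 change (assumed) and let site shifts apply to both arms alike. With 74 per arm, SE ≈ √(2 × (53.8 + s²)/74) and power ≈ Φ(3.9/SE − 1.96).

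| s | SE | Power |
|---|---|---|
| 0 | 1.21 | 89.9% |
| 1 | 1.22 | 89.3% |
| 2 | 1.25 | 87.7% |
| 3 | 1.30 | 84.9% |

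This slightly overstates the loss, because the spread realised among only four sites averages less than s². As a share of the planning variance, s = 2 is 4/53.8 = 7% and s = 3 is 9/53.8 = 17%.

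**4. The same by simulation.** 4,000 runs per setting, both site-size patterns, no centre stratum. Simulation error is about 0.5 points for power and 0.35 for type I error.

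| s (assumed) | Power, planned t-test | Power, centre in model |
|---|---|---|
| 0-1 | about 89-90% | about 88-89% |
| 2 | about 87-88% | about 89% |
| 3 | about 85-86% | about 89% |

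For the planned t-test, bias was about 0 and type I error was 4.5-5.6% throughout. The SD of its estimate rose from about 1.20 to about 1.26 at s = 2 and 1.28-1.29 at s = 3. Averaged over the four settings with s = 0 or 1, power was 89.7% for the t-test and 88.9% with centre, a cost of about 1 point.

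**5. Centre as a stratum.** The existing factors give 2 × 2 × 2 = 8 cells. Four centres would make 32 cells, and 164/32 ≈ 5 patients per cell.

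**The case against.** The strongest reply is that randomisation already deals with this. Allocation is central and 1:1, so centre differences cancel in expectation, and what remains by chance is ordinary sampling error that the t-test's standard error already carries. That stands. A reader might infer that local care is confounded with treatment and biases the result, but the article does not support that reading, and step 4 shows no bias and no inflated type I error.

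A reader might also infer that the comparator is really four different treatments. The article does not say so. It sets the same control visits everywhere, and the intervention shares a semi-structured interview, three-monthly calls and one triage scheme. That care varies between hospitals is an inference from what is left open.

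Differences between raters are a weak ground too. The outcome is a change score, so a stable rater or site level cancels, and the rater is blind to arm.

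It is also fair to say that the gain rests on an assumed between-site SD, that leaving centre out of the strata avoids 32 sparse cells, and that further covariates are often left to an analysis plan, which is not shown here. The last point does not dispose of the matter: the article names the primary test, and that test cannot hold a centre term.

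**Conclusion.** The point holds as a cheap improvement in precision and in visible balance. It is not a threat to validity. With assumed between-site SDs of 2 and 3 points, the planned t-test loses roughly 2 and 4-5 points of power. Putting centre in the model recovers about 1 and about 3 of these. If sites hardly differ, adjustment gains nothing and costs up to about 1 point. These figures depend on assumed between-site SDs and site sizes, since the article gives neither, and on site differences that are shared by both arms.

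The documents do not support calling the allocation defective. Recruitment began in August 2023 and was due to finish in November 2024, and the extra cells would have been very small, so stratifying by centre is not proposed.

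**What to change.** Before unblinding, replace the primary t-test with a linear model of 12-month PDQ-39 change containing arm, centre (four levels, fixed), the three stratification factors (sex, diagnosis, CFS group) and baseline PDQ-39. Add centre to the secondary between-arm models as well. Report the treatment effect by centre descriptively, because a centre main effect does not show whether one site's nurse carries the result. If the full analysis plan already does this, the published description should be brought into line with it.

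The cost is a few lines of analysis wording and three degrees of freedom for centre. Site is known for every patient, so no new data or patients are needed, the sample size of 164 stays, and the randomisation is left as it is.
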